### Target sample size and sampling

#### Retrospective chart review

Data analysis for RCR will use two methods – DiD analysis and interrupted time series (ITS) analysis. For DiD analysis, the sample size was calculated using *clustersampsi* in STATA version 14.2 (StataCorp, 2015).

First for T2DM, 1800 patient visits (900 in each arm) were needed to have 80% power to detect a relative change of 28% in the proportion of the patients receiving an annual HbA1c test from the baseline proportion of 52.5% (Mastura *et al*., 2011). This sample size was calculated while taking into account the estimated cluster effect [intracluster correlation (ICC) = 0.091] (Singh *et al*., 2015; Solorio *et al*., 2015). The minimum sample size was rounded up to 2000 or a cluster size of 50 patient visits per clinic. Therefore, the final target sample size for T2DM was 84 patient visits per clinic, after adjusting for an estimated 40% untraceable records.

Second, for hypertension, 1760 patient visits (880 in each arm) were needed to have 80% power to detect a 28% relative change in the proportion of hypertension patients with at least one lipid profile from the baseline proportion of 46% (Wong *et al*., 2015). This calculation took into account the estimated clustering of this outcome at the clinic level (ICC = 0.076) (Singh *et al*., 2015). After adjusting for 40% potentially untraceable records, the sample size required for hypertension patient visits was also 84 patient visits per clinic.

For ITS analysis, a minimum of 100 patient visits per arm at each time point is needed (Wagner *et al*., 2002). A minimum of eight time points was needed for both before and after intervention. In this study, eight time points pre-intervention and nine time points post 15-month intervention were chosen to evaluate the trend and level change over time. For each clinic, the estimated sample size required is ten patient visits for each disease. The final sample size after accounting for 40% untraceable records was 17 patient visits per clinic for each disease.

Systematic random sampling is used to sample the medical records by creating a sampling frame from the patients’ register either in a paper or in an electronic format. In facilities where neither of these is available, the lists are created from patient appointment books.

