### Data analysis

The data will be analysed using STATA version 14 and R version 3.3.2 (StataCorp, 2015; RStudio Team, 2016; R Core Team, 2017). Descriptive data will be expressed as means or proportions with their corresponding 95% confidence intervals or medians with interquartile ranges. Statistical significance will be determined with a 2-sided *P*-value with *P* < 0.05. A complete case analysis will be used.

An interim analysis will be conducted at the end of Phase 2. A research management team is tasked to monitor the study at the end of Phase 2 and Phase 3b. The research management team will review and comment on the interim and final analysis.

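### The stated hypertension inputs give about 73–75% power, not 80%: baseline 46%, 28% relative change, ICC 0.076 and 880 visits per arm do not fit together

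*Protocol article*

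**What the plan says.** Under Target sample size and sampling, Retrospective chart review, the article introduces two calculations with "For DiD analysis, the sample size was calculated using" a named Stata routine.

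- **T2DM:** 1800 visits (900 per arm) for 80% power to detect a 28% relative change from 52.5%, with ICC 0.091.
- **Hypertension:** "1760 patient visits (880 in each arm) were needed to have 80% power to detect a 28% relative change". The outcome is the proportion of "hypertension patients with at least one lipid profile from the baseline proportion of 46" per cent, and the calculation allows for "estimated clustering of this outcome at the clinic level (ICC = 0.076").

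The minimum for T2DM is rounded up to 50 visits per clinic. For both diseases the target is then 84 per clinic, to allow for 40% untraceable records. Study design and study sites gives 20 intervention and 20 control clinics. Data analysis adds: "Statistical significance will be determined with a 2-sided *P*-value with *P* < 0.05". No target proportion is given in absolute terms, and no pre–post correlation is stated.

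**The concern.** The article prints the baseline, effect, ICC, sample size and power for hypertension, so the calculation can be checked from the page. The T2DM calculation beside it reproduces exactly and the hypertension one does not. Annual lipid testing is the only outcome used to size the hypertension sample, and it is a process-of-care indicator under the primary objective. If the printed set is inconsistent, a reader cannot tell what change the hypertension sample was planned to detect, or with what power.

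**Working it through.** **Inputs.** k = 20 clinics per arm; two-sided 5%; power 80%. T2DM: p1 = 0.525, p2 = 0.525 × 1.28 = 0.672, ICC 0.091, 900/20 = 45 visits per clinic. Hypertension: p1 = 0.46, p2 = 0.46 × 1.28 = 0.5888, ICC 0.076, 880/20 = 44 visits per clinic.

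**Formula.** Effective number per arm: n = (t.975 + t.80)² × [p1(1−p1) + p2(1−p2)] / (p2−p1)². Visits per clinic with k fixed: m = n(1−ICC)/(k − n×ICC). With 38 df, t.975 + t.80 = 2.0244 + 0.8512 = 2.8756, whose square is 8.269. With normal quantiles the square is 7.849.

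**Step 1: reproduce T2DM.** n = 8.269 × 0.46979 / 0.147² = 179.8. m = 179.8 × 0.909 / (20 − 16.36) = 44.9, so 45 per clinic, 900 per arm and 1800 in total, as printed. Power at 45 per clinic is 80.0%. This identifies a formula that fits: unpooled variance, t on 38 df, two arms compared once, no baseline term.

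**Step 2: the same formula for hypertension as stated.** n = 8.269 × 0.49051 / 0.1288² = 244.5. m = 244.5 × 0.924 / (20 − 18.58) = 159.3 per clinic. With normal quantiles, n = 232.1 and m = 90.8. Neither is 44.

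**Step 3: power at the printed size.** Design effect = 1 + 43 × 0.076 = 4.268; effective n = 880/4.268 = 206.2; standardised difference = 0.1288 / √(0.49051/206.2) = 2.641. Power is 72.9% (t) or 75.2% (normal).

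| Traceable visits per clinic | Power, t | Power, normal |
|---|---|---|
| 44 (printed minimum) | 72.9% | 75.2% |
| 50 (rounded) | 74.1% | 76.3% |
| 80 | 77.3% | 79.4% |
| 90 | 77.9% | 80.0% |
| unlimited | 83% | 85% |

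At 44 per clinic, pooled or arcsine variance gives 72.4–74.7%, and a continuity correction gives 69.0–71.4%. Reading the 28% as a decrease gives 70.9–77.0%. Rounding of 46%, 28% or 0.076 gives 72–77%. No two-sided variant comes within 2 points of 80%.

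**Step 4: what would reconcile the figures.**

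- *Target 60%.* n = 8.269 × 0.4884 / 0.14² = 206.0; m = 206.0 × 0.924 / (20 − 15.66) = 43.9, so 44 per clinic and 880 per arm, as printed. The relative change is 0.14/0.46 = 30.4%.
- *A smaller ICC.* With 28% kept, 44 per clinic gives 80% at an ICC of about 0.060 (t) or 0.065 (normal).

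**Step 5: the inflation.** 50/(1 − 0.40) = 83.3, so 84 is right. The increase replaces records that cannot be traced and adds no analysed visits.

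**Step 6: DiD reading, as a sensitivity check.** Let r be the clinic-period autocorrelation, which the article does not give. With m visits per clinic in each period, the variance of the DiD is [(1−ICC)/m + ICC(1−r)]/20 × [3p1(1−p1) + p2(1−p2)].

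| Assumed r | T2DM, m = 45 (t) | Hypertension, 28%, m = 44 (t) |
|---|---|---|
| 0 | 49% | 44% |
| 0.5 | 72% | 64% |
| 0.6 | 78% | 70% |
| 0.8 | 91% | 84% |

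Power reaches 80% at r of about 0.63 for T2DM and about 0.74 for hypertension.

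**The case against.** **The size is small.** The difference is 58.9% against 60.0%, about 1.1 percentage points, and the power shortfall is 5–7 points. This stands, and it limits the severity.

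**44 visits per clinic may not be what is analysed.** The DiD pools eight pre-intervention and nine post-intervention months. If the ten traceable visits per clinic per disease planned for the interrupted time series are per month, each period holds 80–90 visits per clinic. Power is then about 77–80%, and the change detectable with 80% power is 28.0–28.9% relative. This also stands. A reader might infer that the hypertension comparison is seriously underpowered, that more visits cannot help, or that a null result will be misread. The documents do not support that: the ceiling is above 80%, and the article plans to report odds ratios with confidence intervals, which show the precision achieved.

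**The 60% target is inferred.** A reader might conclude that 880 per arm arises only from 46% to 60%, so that the 28% is proven wrong. That holds only if the other printed inputs are right, and an ICC near 0.060–0.065 would serve equally well. One-sided testing would give 81–84%, but Data analysis specifies two-sided tests and T2DM reproduces without a one-sided assumption.

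**The DiD label.** A reader might infer that both figures can only be post-period comparisons and that true DiD power is far below 80%. That is not shown. The DiD powers of 44–91% depend on a correlation the article does not give, and a DiD can also reach 80%. A post-period comparison is simply the plainest reading, because T2DM reproduces exactly with no baseline term. A DiD reading would need a different correlation for each disease to give 80% at the printed sizes.

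**Conclusion.** The concern holds in a limited form. The printed hypertension baseline, effect, ICC, sample size and power cannot all be right together. With 20 clinics per arm and two-sided 5% testing, 880 visits per arm give about 73% (t) or 75% (normal) power for 46% to 58.9%, and 74–76% at 50 per clinic. A 28% figure carried over from T2DM is the likeliest cause, because the formula that reproduces T2DM exactly also reproduces 880 for a 60% target, but a misreported ICC cannot be excluded. These results rest on a two-arm comparison at one period with equal cluster sizes. The basis of both chart-review calculations (post-period or DiD) is unclear and needs stating; it is not a shown error. The correction should be made, but no outcome, analysis or recruitment target changes.

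**What to change.** Check the inputs used in the original run, then restate the hypertension calculation in whichever form is true:

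- 80% power to detect 46% to 60% (30.4% relative) with 880 visits per arm, if the authors confirm that target; or
- about 73–75% power for a 28% relative change with 880 per arm, adding that it is about 77–80% if 80–90 traceable visits per clinic per period are analysed; or
- the corrected ICC, if that is the misprint.

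Give the target proportion in absolute terms. Add one sentence saying whether the two chart-review calculations are for a post-period two-arm comparison or for the DiD and, if the latter, state the assumed pre–post correlation.

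The cost is wording only, with no extra clinics or visits. If the effect or power is the misprint, the stated detectable change or power becomes slightly less favourable.

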#### Patient exit survey

For the patient exit survey, we aim to detect a 15% change in the proportion of patients who would recommend the clinic to family or friends, while accounting for an estimated ICC from a previous study of 0.116 (Sivasampu *et al*., 2016). With a statistical power of 80%, we would require at least 920 patient surveys (460 in each arm). Hence, the data collection teams aim to recruit 23 patients per clinic. Patients are sampled consecutively using convenience sampling until the required numbers are achieved.

#### Provider survey

All clinic staff who meet study inclusion criteria will be interviewed. All visiting staff who visit the clinic on a regular schedule are also included in the survey. As EnPHC interventions would involve a change in clinic flow and staff allocation, it is necessary to measure the change in numbers for all categories of staff.

### Data analysis

The data will be analysed using STATA version 14 and R version 3.3.2 (StataCorp, 2015; RStudio Team, 2016; R Core Team, 2017). Descriptive data will be expressed as means or proportions with their corresponding 95% confidence intervals or medians with interquartile ranges. Statistical significance will be determined with a 2-sided *P*-value with *P* < 0.05. A complete case analysis will be used.

An interim analysis will be conducted at the end of Phase 2. A research management team is tasked to monitor the study at the end of Phase 2 and Phase 3b. The research management team will review and comment on the interim and final analysis.

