The conceptual framework to guide the implementation and evaluation is discussed below. An impact evaluation that spans from the community to the patients and providers of primary healthcare is carried out (Institute for Public Health, 2019a). To further strengthen the findings from the impact evaluation studies, a process evaluation study is carried out to evaluate the implementation process in terms of fidelity and quality of implementation (Institute for Health Systems Research, 2019).

To evaluate the interventions, complementary data from multiple sources are used to measure outcomes. Evaluation performed at primary healthcare clinics aims to measure health service and patient outcomes. Therefore, the primary objective is to evaluate the impact of EnPHC interventions on processes of care and intermediate clinical outcomes among T2DM and hypertension patients, and the secondary objective is to evaluate the impact of the EnPHC interventions on patients’ experience and providers’ job satisfaction. The aim of this paper is to describe the sequential steps taken to evaluate the EnPHC interventions at primary healthcare clinics (EnPHC-EVA: Facility) and the methods used.

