### Outcome measures

Outcome measures used in this study are captured using different data collection tools and are summarised in Table 4. It is anticipated that improvements of blood pressure, lipid levels and glycaemic control will be observable after at least one year as changes have been detected after 12.5 months of implementation in similar evaluation studies (Norris *et al*., 2001). Hence, for post-intervention, information on processes of care (investigations, counselling and prescribing patterns) will be gathered via RCRs 15 months after implementation.

**Table 4. tbl4:** Outcome measures of the EnPHC-EVA: facility study

Outcomes	Indicators		Data Source
	T2DM	Hypertension	
Process of care	Proportion of Patients whose BP and glucose were measured at every visit Patients with HbA1c tests done at least once over the past three months Patients with weight and BMI assessed at least once over the past six months Patients with the following examinations done at least once a year: lipid profile tests, serum creatinine, blood urea nitrogen and urine albumin tests, eye examination (visual acuity and fundus), foot examination and liver function test Patients with cardiovascular risk assessment done within the past one year Patients who received counselling: exercise, dietary Patients who received pharmacotherapy: lipid lowering drugs, insulin and antihypertensives	Proportion of Patients with BP measured at every visit Patients with fasting blood glucose, serum creatinine, urine albumin and lipid profile measured at least once a year Patients with electrocardiogram and cardiovascular risk assessment done within the past one year Patients who received counselling: exercise, dietary Patients who received pharmacotherapy: antihypertensives	RCR
Intermediate clinical outcomes	Proportion of Patients with HbA1c ≤ 7% Patients with BP ≤ 135/75 mmHg Patients with LDL-C ≤ 2.6 mmol/L Patients with HDL-C > 1.0 mmol/L (male) or HDL-C > 1.2 mmol/L (female)	Proportion of Patients with BP < 140/90 mmHg Patients with LDL-C ≤ 2.6 mmol/L Patients with HDL-C > 1.0 mmol/L (male) or HDL-C > 1.2 mmol/L (female)	RCR
Patient disease awareness	Proportion of patients who know their diagnosis		Patient exit survey

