There are several limitations in this study. First, it is not possible to distinguish the effects from each activity of the intervention as it is a complex intervention. Next, the findings of this study will only be generalisable to clinics with similar characteristics. Long-term outcomes such as micro- and macrovascular complications and behavioural changes could not be measured as the study duration is not sufficient to observe these changes. Missing data arising from untraceable records and incomplete documentation in medical records may introduce bias to the findings. This could be improved by integrated electronic information systems in the long run.

In summary, this study will provide evidence on the effectiveness of a complex intervention designed to reduce the number of undiagnosed T2DM and hypertension patients as well as improve the overall quality of care in this group of patients to delay overall disease progression.

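### Complete-case analysis limits HbA1c, LDL-C and HDL-C control to tested patients, so a rise in testing can move the control estimates with no change in any patient

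*Protocol article*

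**What the plan says.** Data analysis fixes one missing-data rule for the whole study, with no exception by outcome: "A complete case analysis will be used".

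Table 4 (Outcome measures) takes the intermediate clinical outcomes from the chart review. They include "Patients with HbA1c ≤ 7" (per cent) for T2DM, and "Patients with LDL-C ≤ 2.6 mmol/L" and an HDL-C threshold for both diseases. The table gives no rule for a patient without a result.

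The same table makes testing an outcome. For T2DM it lists "Patients with HbA1c tests done at least once over the past three months" and an annual lipid profile. For hypertension it lists "Patients with fasting blood glucose, serum creatinine, urine albumin and lipid profile measured at least once a year". Both kinds of outcome carry equal rank in the Introduction: "the primary objective is to evaluate the impact of EnPHC interventions on processes of care and intermediate clinical outcomes".

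Target sample size and sampling sizes the study on a 28% relative change in annual HbA1c testing from 52.5% (T2DM) and in lipid testing from 46% (hypertension). The Discussion makes clear that improvement in care processes is the aim. Its limitations paragraph adds: "Missing data arising from untraceable records and incomplete documentation in medical records may introduce bias to the findings". That sentence names lost or incomplete records. It does not mention tests that were never done.

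**The concern.** A patient with no HbA1c or lipid result has no value for the control outcome and drops out of a complete-case analysis. Who remains depends on testing and recording, and the package is built to change both. Besides aiming at better guideline adherence, it adds a visit checklist that captures laboratory results, a standardised NCD care form and more frequent audits (Table 1). The set of patients who enter the control analysis may therefore change between periods, and by more in the intervention arm.

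DiD removes fixed differences between arms and changes common to both. It does not remove a change in the mix of tested patients that starts with the intervention in one arm more than the other. The parallel-trends and baseline-equivalence checks look at the time before the start and cannot detect it. The interrupted time series uses the same tested-only results.

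At stake is the clinical half of the primary objective. A reported gain or loss in glycaemic or lipid control could reflect who was tested, and the stated analysis would not separate this from a change in control. The project is meant to inform a decision on national expansion.

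**Working it through.** **1. The plan's own figure.** The T2DM sample size fixes what change in testing the study was built to detect. Inputs: 52.5% baseline, 28% relative change (0.525 × 1.28 = 0.672 if upward), ICC 0.091, k = 20 clinics per arm, 80% power, two-sided 5%.
- Individual-level n per arm, unpooled variance, t quantiles on 38 df: (0.525×0.475 + 0.672×0.328) × (t₀.₉₇₅ + t₀.₈₀)² / 0.147² = 179.8.
- Visits per clinic: m = n(1 − ICC)/(k − n×ICC) = 179.8×0.909/(20 − 179.8×0.091) = 44.9, so 45 per clinic and 900 per arm, as stated.

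**2. Share without a result.** On the protocol's annual testing rates, 47.5% of T2DM patients would lack an HbA1c at baseline, and 54% of hypertension patients would lack a lipid result. Of 50 traced visits per clinic, about 26 (50 × 0.525) and 23 (50 × 0.46) would be evaluable. After a 28% relative rise the numbers are about 34 (50 × 0.672) and 29 (50 × 0.589). The HbA1c indicator in Table 4 uses a three-month window, so the share without a result could be larger under that window.

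**3. Shift from selection alone.** Let t₀ and t₁ be the share tested before and after, c the control rate in patients who would be tested in either period, and cₙ the rate in the newly tested. With no patient's control changed:

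observed control after = [t₀c + (t₁ − t₀)cₙ]/t₁.

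The newly tested make up (0.672 − 0.525)/0.672 = 21.9% of those tested, so the shift is 0.219 × (cₙ − c). If testing and control stay flat in the control arm, the DiD odds ratio is the after-versus-before odds ratio in the intervention arm. The values of c and cₙ are assumptions.

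| c | cₙ | Observed after | Shift (points) | DiD OR |
|---|---|---|---|---|
| 25% | 15% | (0.525×0.25 + 0.147×0.15)/0.672 = 22.8% | −2.2 | 0.89 |
| 25% | 25% | 25.0% | 0 | 1.00 |
| 25% | 35% | (0.525×0.25 + 0.147×0.35)/0.672 = 27.2% | +2.2 | 1.12 |
| 25% | 5% | 20.6% | −4.4 | 0.78 |
| 25% | 45% | 29.4% | +4.4 | 1.25 |
| 40% | 10% | 33.4% | −6.6 | 0.75 |
| 30% | 60% | 36.6% | +6.6 | 1.34 |

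Lipid testing in hypertension (46% to 58.9%) gives the same shifts, because the relative rise is the same.

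**4. Contamination.** Suppose testing in control clinics rises half as much, to 59.85%. With c = 25% and cₙ = 35%, the control arm shows (0.525×0.25 + 0.0735×0.35)/0.5985 = 26.2%, a shift of 1.2 points. The net DiD shift falls from 2.2 to about 1.0 point.

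**5. Counting the untested as not controlled.** With 25% control in everyone tested, the share tested and at target goes from 0.525×0.25 = 13.1% to 0.672×0.25 = 16.8%, an OR of (0.168/0.832)/(0.13125/0.86875) = 1.34. Testing alone produces this, so that measure does not solve the problem.

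**The case against.** Four points on the other side have force.

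- A reader might infer that control is biased simply because missingness varies by arm and period. The documents do not support that. Arm, period and their interaction are the terms of the DiD model, and missingness that depends only on model terms does not bias a complete-case regression. Bias also needs testing to depend on control status, given the covariates, in a way that differs by arm and period. The model does adjust for patient- and clinic-level covariates (Appendix F, not shown), which would remove the part of the difference that they explain.
- A reader might also infer that the denominator will change in one arm only, or that the sample size forecasts 67.2%. The sample size section gives a detectable relative change, with no direction and no forecast. The Intervention checklist section expects contamination of the control clinics.
- The size rests on assumed control rates. A 2.2-point shift is below one DiD standard error: with 525 tested in each of three arm-period cells, 672 in the fourth and 25% control, √[0.1875 × (3/525 + 1/672)] = 3.7 points, before any allowance for clustering.
- Testing rates are reported anyway as process outcomes, the limitations paragraph concedes possible bias from missing data, and sensitivity analyses are often left to a fuller document.

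All four limit the claim, and none removes it. Adjustment covers measured covariates only. The concession concerns records, not absent tests. Complete-case analysis is the method the article states, not a detail it leaves open.

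**Conclusion.** The point holds as a conditional one. The stated analysis restricts HbA1c, LDL-C and HDL-C control to patients with a result, in a study that aims to change how many have one, and nothing in the article separates a change in who is tested from a change in control. The resulting shift is about 2.2 points (OR 0.89 or 1.12) for a 10-point gap at 25% control, and runs from −6.6 to +6.6 points (OR 0.75 to 1.34) over the wider assumed rates. These figures assume that testing rises by the full 28% in the intervention arm and not in the control arm, that patients tested under existing practice continue to be tested, and that covariates explain none of the gap. The sign cannot be told from the documents, and zero lies within the range. Blood pressure control is left out: its process indicator is measurement at every visit, and the testing rates used here do not apply to it.

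**What to change.** For the HbA1c and lipid control outcomes:

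1. State the denominator of each outcome, and report the share with a result by arm and period next to each control estimate.
2. Add an analysis of all traced eligible patients, by multiple imputation or inverse-probability-of-testing weighting, that uses auxiliary chart variables beyond the outcome-model covariates (for example glucose, treatment, comorbidity, and earlier results where recorded). With the model covariates alone it would nearly reproduce the complete-case result.
3. Add bounds, or a delta-adjusted analysis over a stated range of control in the untested, since step 2 still assumes that recorded variables explain testing.
4. Claim improved control only if the conclusion holds across these analyses.
5. Report the proportion tested and at target descriptively only, outside the rule in step 4, because it rises with testing alone.

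This addresses traced patients without a result. It does not address untraceable records. The cost is extra analysis work on chart data, somewhat wider intervals and a more cautious claim about control.
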